### Inclusion/Exclusion criteria

Participants will be considered eligible for participation based on the following criteria:

Children with CP aged ≤5 years, from an ultra-poor family (as classified by the World Bank i.e. per day per capita income <1.90 USD; [35]) and registered in the BCPR. The BCPR registers children with CP following the case definition adopted from the Surveillance of CP in Europe (SCPE) and the Australian CP Register (ACPR) [3].Primary caregiver (e.g. parent, sibling, grandparent of the child with CP)Primary caregiver has the capacity to give informed consent and is willing to take part in the study including microfinance/livelihood arm along with their child with CP.

Participants will be considered ineligible for participation based on the following criteria:

Currently in receipt of microfinance/livelihood support from another source.Currently participating in any other clinical trial or intervention program.

The BCPR findings show that 34.2% of the children registered are aged <5 years and 97% of the families are ultra-poor [3]. Considering the number of registrants from Shahjadpur (i.e.~1125), there are ~373 children eligible to participate in the study. Therefore, recruitment of 210 children and their primary caregiver in the trial (<60% of the available pool) is feasible. Sociodemographic, economic, and health data of these children and their families are already recorded in the BCPR allowing quick identification and recruitment. All families enrolled in the BCPR have also been mapped using Geographic Information System (GIS) (Fig 2).

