### Sample size calculation

The sample size for this cluster RCT has been computed based on methods described in Donner et al. [36]. We made several assumptions from the existing knowledge about the study population while calculating the sample size for this cluster RCT. Specifically, our sample size calculation is balanced between a standard statistical power and a pragmatic study setting. Based on our pilot data and existing literature we predict a 35% improvement of HRQoL in the IMCBR group, 20% improvement in the CBR alone group, and 5% improvement in the care-as-usual group [9]. A homogeneous study population will allow us to balance randomisation considering intra-cluster correlation of 0.5 and coefficient of variation in cluster size of 0.5.

Based on the calculation, we will recruit seven clusters in each arm (allocating 1:1:1), and each cluster will consist of 10 children with CP- primary caregivers dyads totalling 21 clusters of 210 dyads. With a sample size of 210 dyads, this study will have 80% statistical power to detect these effects (two-sided α-value = 0.05). Power calculation took into account up to 20% sample attrition by the end of the trial.

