### Cluster formation and randomisation

The study will include 21 clusters randomised to three arms (7 clusters each) and allocated by a 1:1:1 ratio. While deciding the allocation ratio of 1:1:1 we considered the number of children with CP available in the BCPR sampling frame as well as the high mortality rate among children with CP below five years of age [37]. Each cluster will come from a ‘Mouza’, the smallest public administrative unit in Bangladesh comprising of approximately five villages (~8,250 people) and will include 10 CP child-primary caregiver dyads. In order to minimise ‘contamination’ of the intervention types, clusters will be separated from each other by buffering areas comprising villages not taking part in the study. Cluster margins will be configured so that they align with natural divisions that separate residents in the community (e.g. rivers). The randomisation process will be executed following the standard process.

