### Trial monitoring

An independent Data Safety and Monitoring Board (DSMB) has been formed for this trial. The members of DSMB will meet monthly to monitor the safety of trial participants and the quality of trial data. The Chair of the DSMB will report to the Chief Investigator regarding issues related to data safety, quality of intervention and serious adverse event.

A serious adverse event will be defined as any event that results in injury, requires inpatient hospitalisation or prolongation of existing hospitalisation, or death or results in a persistent or significant disability or incapacity.

The DSMB will conduct a blinded interim analysis of effectiveness and safety endpoints once 210 participants have completed the trial. The DSMB may recommend continuing the trial, early termination of the trial, or modification of the trial. A recommendation to terminate the trial early will be made if there is clear evidence of a clinically harmful effect. The trial will not be stopped early on the grounds of futility.

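### The interim analysis is triggered at 210 completers, which is the whole planned sample, so it is either never reached or reached only when the trial is over

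*Protocol article*

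**What the plan says.** Under Trial monitoring, the protocol article sets the timing of the interim look: "The DSMB will conduct a blinded interim analysis of effectiveness and safety endpoints once 210 participants have completed the trial". It then lists three recommendations open to the board: carry on, change the trial, or end it early. The ground for ending early is harm: "A recommendation to terminate the trial early will be made if there is clear evidence of a clinically harmful effect". Stopping for futility is ruled out. The same section also has the DSMB meeting every month on participant safety and data quality, with its Chair reporting serious adverse events to the Chief Investigator.

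The planned size appears in several places. Sample size calculation: "each cluster will consist of 10 children with CP- primary caregivers dyads totalling 21 clusters of 210 dyads". Cluster formation and randomisation: "The study will include 21 clusters randomised to three arms (7 clusters each) and allocated by a 1:1:1 ratio". Inclusion/Exclusion criteria: "recruitment of 210 children and their primary caregiver in the trial (<60% of the available pool) is feasible". The Abstract gives the same total.

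On losses, Sample size calculation says: "Power calculation took into account up to 20% sample attrition by the end of the trial". Cluster formation and randomisation, explaining the allocation ratio, refers to "the high mortality rate among children with CP below five years of age".

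**The concern.** An interim analysis is useful only if it happens while something can still be decided. Here the number that triggers it is the number of dyads to be recruited, and the condition is that they have completed. Followed literally, the rule gives an analysis that does not take place, or one that coincides with the final analysis. Yet the section presents it as the basis for a recommendation to continue, modify or stop.

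The participants are children aged 5 years or under from ultra-poor families, in a population whose mortality the article itself describes as high. An ethics committee or funder reading the section would count this look as a working safeguard.

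**Working it through.** **Inputs**
- Arms 3, clusters per arm 7 (Cluster formation and randomisation).
- Dyads per cluster 10, attrition up to 20% (Sample size calculation).
- Trigger: 210 completed (Trial monitoring).
- Intervention 12 months (Abstract); last assessment at 18 months (Outcome measures).

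**Step 1: reproduce the planned total.** 3 × 7 × 10 = 210 dyads, as stated.

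**Step 2: position of the trigger.** 210 / 210 = 100% of the planned sample.

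**Step 3: completers after attrition.** Completers = 210 × (1 − d), where d is the proportion lost. Assuming dyads drop out independently, the chance that all 210 complete is (1 − d)^210.

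| d | Completers | Chance that all 210 complete |
|---|---|---|
| 0% | 210 | 1 |
| 1% | 207.9 | 0.12 |
| 5% | 199.5 | 2 × 10⁻⁵ |
| 10% | 189 | 2 × 10⁻¹⁰ |
| 20% | 168 | 4 × 10⁻²¹ |

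At the 20% ceiling the shortfall is 210 − 168 = 42. Because the article says up to 20%, 168 is the lowest number planned for, not a forecast. Independence is a simplification: losses that cluster together would change the probabilities. The conclusion does not need them, because one loss leaves 209 and the trigger unmet.

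**Step 4: enrolment needed to reach the trigger.** At 20% attrition, 210 / 0.80 = 262.5, so 263 dyads would have to be enrolled for 210 to complete. The plan is to enrol 210.

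**Step 5: the zero-loss case.** If nobody is lost, the 210th completion is that of the last dyad. Taking completion to mean the 18-month assessment, every dyad is then through its 12 months of intervention and all follow-up. Nothing remains to continue, modify or stop.

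**Step 6: the other way to count.** If children and caregivers were counted separately, the total would be 2 × 210 = 420 individuals, and 210 would be 50%, or 105 dyads. At 20% attrition 420 × 0.80 = 336 individuals would complete, so this trigger could be reached.

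**The case against.** The strongest defence is the count of individuals in Step 6: the trigger would then be a genuine halfway look. The article gives no enrolment timetable, so one cannot show that the remaining dyads would be off intervention by then. But it never says that individuals are being counted and never gives a total of 420. Wherever else it uses 210, it means dyads or children. The reading is possible but not supported. If it was intended, the sentence needs the unit stated.

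A second defence is that safety oversight does not hang on this analysis. That stands. The board meets monthly on safety, and the sentence on terminating for harm is not tied to the interim look alone. A reader might infer that the trial has no real means of stopping early for harm; the document does not support that.

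A reader might also infer from the word blinded that the board would see only data pooled over arms, and so could not detect harm in one of them. The article does not say this. Arms shown under masked codes would also count as blinded and would let such harm be seen. How data are shown to the board is a matter for its charter, and no fault is claimed here.

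Finally, the flaw does not touch the sample size, the primary estimate or the final analysis. That is correct and limits its reach. It does not make the trigger workable.

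**Conclusion.** The point holds as a contradiction between a stated rule and the stated sample size. The interim trigger equals 100% of the 210 planned dyads. Any loss, from one dyad up to the 42 that the plan allows for, means it is never reached; zero loss means it is reached only at the end. This analysis therefore cannot serve the recommendations attached to it. A fuller protocol might add detail, but it could not turn 210 completers out of 210 dyads into an interim point.

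The conclusion rests on one assumption about wording: that participants in the trigger sentence are the dyads or children to which 210 refers elsewhere. It extends to this interim analysis only, not to the monthly DSMB review.

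**What to change.** Reconcile the trigger with the planned sample in one of two ways.

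1. Keep an interim look. Restate the trigger as a point reached while the intervention is still running, and name the unit. One example is a stated fraction of the 210 dyads having had the 6-month assessment, which is already scheduled. Limit this look to safety endpoints, so that no alpha is spent on effectiveness.
2. Drop it. Delete the interim-analysis sentence and state that any recommendation to terminate early for harm rests on the monthly DSMB safety review.

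The cost is a short protocol amendment and, under the first option, one small extra report to the DSMB. The sample size does not change.

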### Intervention

#### Arm A- Integrated Microfinance/livelihood and Community-Based Rehabilitation (IMCBR)

Participants randomised to IMCBR arm will be supported to create microfinance/livelihood groups (10 CP child-primary caregiver dyads per group). The groups will be formed voluntarily along geographical boundaries to facilitate participation, retention, and meeting logistics. Each cluster will meet weekly to discuss microfinance/livelihood activities (e.g. weekly credit collection and troubleshooting) (90 minutes) and for CBR with children with CP comprising early intervention and primary caregiver’s education (90 minutes).

*A*.*1 Microfinance/livelihood program details*. Group meetings will be organised with members of each cluster to discuss (i) details of the program, (ii) potential benefits and challenges of participation in the program, and (iii) motivations for participation. Participants of each cluster can then apply for a loan/livelihood support; a minimum 10% deposit of the requested loan/livelihood support amount in the form of savings is required and is admissible immediately after cluster formation. Once the application is completed, loan approval and disbursement of the loan will occur approximately within one week. The loan disbursement and collection of repayment will be managed by a local microfinance organisation. However, the funds required for the loan will be reimbursed from the study budget at the end of loan disbursement.

Amount, return cycle of loan and investment areas: Each of the ultra-poor families will receive a loan/livelihood support amounting/equivalent to ~100–300 AUD at a 12% flat interest rate. The return cycle will be one year with a weekly repayment schedule. Common investment areas for the ultra-poor loan will be for goat or cattle rearing, seeds for agriculture, home-based weaving, and handicraft business [38].

*A*.*2 CBR*. There will be two major components of the CBR program, which will occur during cluster meetings following the microfinance/livelihood portion.

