## Results (pilot data)

We have piloted the activities of the proposed trial in the study area to determine the feasibility of the trial. The aim of the pilot study was to assess the acceptance rate and repayment rate of microfinance program among primary caregivers of children with CP. During the pilot phase, 20 ultra-poor families form the BCPR cohort (recruited between Jan 2015 and Nov 2018, n = 1,381) were identified who already have accessed microfinance from different local NGOs. The amounts of microfinance loan borrowed varied between ~100–300 AUD with 12-month loans payable in 45–46 weekly instalments. Of these families, the majority (n = 12) took loans to start/enhance income-generating activities (e.g. agricultural work, purchasing livestock, vehicle for hire, etc.). About 50% of borrowers repaid their first weekly instalment while the repayment schedule for the rest of the respondents was not due at the time of data collection.

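### Loan-related harm in Arm A is neither a named adverse event nor a named ground for stopping, so monitoring would pick it up only indirectly

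*Protocol article*

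**What the plan says.** The protocol article describes Arm A's credit in part A.1 of the Intervention section: "Each of the ultra-poor families will receive a loan/livelihood support amounting/equivalent to ~100–300 AUD at a 12% flat interest rate". On timing it says "The return cycle will be one year with a weekly repayment schedule", and before borrowing "a minimum 10% deposit of the requested loan/livelihood support amount in the form of savings is required". The records sit outside the trial team: "The loan disbursement and collection of repayment will be managed by a local microfinance organisation". Arm B receives the same rehabilitation sessions without the microfinance/livelihood component. Under Inclusion/Exclusion criteria, families must live on less than 1.90 USD per person per day.

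The Trial monitoring section defines a serious adverse event as "any event that results in injury, requires inpatient hospitalisation or prolongation of existing hospitalisation, or death", or lasting or significant disability or incapacity. On stopping it says: "A recommendation to terminate the trial early will be made if there is clear evidence of a clinically harmful effect". The DSMB meets monthly on participant safety and data quality. Its interim analysis is set for when 210 participants have completed the trial.

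The outcome sections list family income and expenditure, household assets, two food-security scales, and caregiver mental health, quality of life and social capital, all at baseline, 6, 12 and 18 months. They do not list repayment, arrears or default.

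**The concern.** The monitoring rules suit a rehabilitation trial. What Arm A adds over Arm B, however, is a programme built on interest-bearing credit, and the foreseeable harms of credit are financial: missed instalments, default, selling assets or borrowing elsewhere to repay, and leaving the group because of arrears. None of these is in itself an injury, a hospitalisation, a death, a disability or a clinical effect.

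Two things are at stake. The first is the protection of borrowers while loans are running. The second is what the trial can conclude. The Introduction plans scale-up through microfinance organisations if the programme works, and those organisations will need to know how many families fell behind.

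There is also a link to the main comparison. In Arm A the rehabilitation session follows the microfinance session at the same weekly meeting. A family that stays away to avoid collection could also miss the child's therapy. Debt-related withdrawal would then be both a harm and a form of attrition specific to Arm A.

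**Working it through.** The point is mainly qualitative. The arithmetic sizes the exposure and checks whether other parts of the plan fill the gap.

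1. **Foreseeable harm against the stated rules.** Arrears, default, sale of assets or new borrowing to repay, and debt-related withdrawal meet neither the serious adverse event definition nor the termination criterion. None is a listed outcome. An extreme consequence, such as a hospitalisation, would count.

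2. **Does the interim analysis help?** Planned sample: 3 arms × 7 clusters × 10 dyads = 210, which reproduces the article's figure. The interim trigger is also 210 completers, so 210/210 = 100% of the sample. With the 20% attrition allowed under Sample size calculation, completers number 210 × (1 − 0.20) = 168 and the trigger is not reached. Without attrition it falls after the 12-month intervention. Either way it comes too late to protect borrowers.

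3. **Do the secondary outcomes help?** Partly. They could show an average worsening in Arm A. But none is described as measuring debt or repayment, an arm mean can improve while a minority of families end worse off, and only the 6-month visit falls well inside a one-year loan. The article does not say that the DSMB receives these data during the trial.

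4. **Exposure.** 7 clusters × 10 dyads = 70 families in Arm A. This is an upper limit, because support may not always be a loan.

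5. **Instalment for a family that borrows.** Weekly payment = loan × 1.12 / 52.
   - 100 AUD: 112/52 = 2.15 AUD a week.
   - 300 AUD: 336/52 = 6.46 AUD a week.
   - Solving 100 = (112/52) × [1 − (1 + r)^−52] / r gives r ≈ 0.437% a week, a nominal 22.7% a year on the declining balance. With the 45–46 instalments of the pilot loans it would be 25.6–26.2%.

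6. **Share of income at the eligibility ceiling.** Share = weekly payment / (1.90 USD × 7 days × household size × exchange rate). The exchange rate is not in the article; 1.4 AUD per USD is assumed.
   - 8 people, 100 AUD loan: 2.15 / 148.96 ≈ 1.4%.
   - 4 people, 300 AUD loan: 6.46 / 74.48 ≈ 8.7%.
   - Study location implies 561,076 / 70,998 = 7.9 people per household, which gives about 1.5% to 4.4%.
   - Varying the rate over 0.65–0.75 USD per AUD, with 4 to 7.9 people, gives about 1.3% to 9.1%.
   - Families below the ceiling carry a larger share. Any return on the activity funded by the loan is ignored.

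7. **What the pilot tells us.** Its aim included the repayment rate. For 20 families it reports: "About 50% of borrowers repaid their first weekly instalment while the repayment schedule for the rest of the respondents was not due". With 45–46 instalments per loan, that says nothing about default over a full cycle. These families already held loans from other sources, whereas the trial excludes families currently receiving such support.

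**The case against.** The strongest reply is that the trial is not blind to financial harm. Income and expenditure, assets, food security and caregiver distress are measured repeatedly, and the 18-month visit falls after a one-year loan begun near the start. Weekly meetings deal with instalments and repayment problems, so staff would hear of trouble. The DSMB's safety remit is not limited to clinical events, its chair also reports on intervention quality, and it may recommend modifying the trial without any clinical condition. The stopping sentence says when termination will be recommended; it does not say that no other ground is allowed. All of this stands. A reader might infer that loan harm could be neither seen nor acted on, and the article does not support that.

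Other stronger readings also fail. The loan is not the only thing unique to Arm A: the arm also has a separate 90-minute weekly session, peer groups and savings. Not all 70 families need owe 112–336 AUD, because the text speaks of loan or livelihood support for which participants can apply. The pilot reports no missed instalment, so it is uninformative about default rather than evidence of it.

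Finally, a condensed article may leave a fuller harms plan and the DSMB's data feeds to documents not shown. That is fair as to what is missing. It does not answer the definition and the criterion that the article does state, both of which are clinical.

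**Conclusion.** The point holds in a limited form. The stated serious adverse event definition and the only named ground for early termination are too narrow for the component that separates Arm A from Arm B, and repayment or default is not a listed outcome. Loan-related harm would be visible only indirectly, and nothing in the article says that the DSMB would see it in time.

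Up to 70 families are exposed. Instalments of 2.15–6.46 AUD a week assume a loan of 100–300 AUD repaid in 52 equal payments. The share of income, about 1.4% to 8.7% at the ceiling or 1.5% to 4.4% at the area's mean household size, rests on the assumed exchange rate and household sizes. The conclusion does not depend on it. The default rate is unknown. The primary analysis is not wrong on this account; the gain is in participant safety and in what can be said about scale-up.

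**What to change.** In Trial monitoring:

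- Name loan-related harm as a monitored category: arrears, default, sale of assets or new borrowing to repay, and withdrawal because of debt.
- Have the microfinance organisation's repayment records sent to each monthly DSMB meeting.
- Reword the harm criterion so that it covers harm to the caregiver or household as well as clinical harm. Any threshold for action is for the sponsor and the DSMB to set.

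In the results, report repayment and default by cluster beside the effectiveness findings.

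The cost is small: wording in the protocol and any DSMB charter, a few questions at existing visits, and slightly more reporting. The repayment records should exist in any case, because the microfinance organisation manages weekly collection.

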### Consent and ethical approval

The trial has been approved by the Human Research Ethics Committee (HREC) of the Asian Institute of Disability and Development (Reference number: Southasia-hrec-2019-5-03) and the National Research Ethics Committee (NREC) of Bangladesh Medical Research Council (BMRC) (Reference Number: BMRC/NREC/2016-2019/251; Registration Number: 224 17 06 2019). The study has also been registered at the Australian New Zealand Clinical Trials Registry (ANZCTR) (reg number: ACTRN12619001750178). Informed written consent will be obtained from primary caregivers of children with CP before enrolling into the trial.

